#### Outcomes

##### Primary outcome

We hypothesise that participating in the self-management course will strengthen the participants’ engagement and their knowledge of health resources, and will consequently lead to a higher level of patient activation. Therefore, the primary outcome is patient activation assessed with the patient activation measure (PAM) [48].

PAM contains 13 items representing statements to which the participants indicate their level of agreement on a four-point scale from strongly disagree to strongly agree [48]. The responses give a raw score from 13 to 52, which is calibrated to a total score between 0 and 100 using the transformation tables provided by Insignia Health [49]. A high score indicates that the participants are more activated to adopt and maintain healthy behaviours and self-management of their illness, even under stress [50].

Several studies show that PAM is useful for assessing patient engagement in the management of chronic illness and it has been shown to be sensitive to change in several groups and populations [51–54]. PAM has been translated and validated for use in a Norwegian context [55].

##### Secondary outcomes

Furthermore, we hypothesise that participating in the self-management course may influence several health dimensions leading to the following secondary outcomes:*Pain*: The Brief Pain Inventory [56] will be used for assessing pain. This instrument has four questions related to pain severity and seven questions assessing pain interference [56, 57]. The instrument is widely used for measuring both malignant and non-malignant pain [58, 59] and has been translated and validated for use in a Norwegian context [60–62].*Pain*: The overall experience of pain during the last week will be assessed with a one-item 100-mm visual analogue scale (VAS). The scale’s anchoring points are no pain (0) to intolerable pain (100) [63]. The VAS scale is widely used in the assessment of various conditions and has been validated and found reliable in the assessment of chronic pain [63].*Pain-related self*-*efficacy*: Self-efficacy refers to the person’s self-conception of confidence to complete activities, recognised as a central aspect in the self-management of pain [64]. We will use the Pain Self-Efficacy Questionnaire [64, 65], which has recently been translated into Norwegian [66]. It is a ten-item instrument that ascertains the individual’s level of confidence to live a normal life despite pain. Each question is scored on a scale from 0 to 6 giving a total range of 0–60, with a higher score indicating higher pain self-efficacy [64]. The scale has shown strong psychometric qualities [64, 67].*Anxiety and depression*: The self-rating instrument Hospital Anxiety and Depression Scale (HADS) will be used to assess anxiety and depression [68]. HADS consists of 14 items divided into two subscales, for anxiety and for depression, respectively. Each item is rated from not experiencing a symptom (0) to experiencing a symptom nearly all the time (3), giving a total score range for each subscale from 0 (best) to 21 (worst). Higher scores indicate more severe depression or anxiety [68]. HADS has been translated into Norwegian and has been found to be valid and reliable for use in a Norwegian context [69, 70]. The instrument has shown good validity and reliability for patients with musculoskeletal pain [71].*Quality of life*: We will use the EuroQoL (EQ-5D-5 L) to assess health-related quality of life, comprising the five dimensions of mobility, self-care, usual activities, pain/discomfort and anxiety/depression. In this trial, we will use the new version of the questionnaire, which provides five levels for answering each dimension: no problems, slight problems, moderate problems, severe problems and extreme problems. The scores provide a value based on a population tariff where 0 equates to dead and 1 equates to full health [72, 73]. The instrument has been validated in similar populations [74, 75] and in a Norwegian context [76].*Well-being*: To measure the overall experience of well-being, the Arizona Integrative Outcome Scale (AIOS) will be used [77]. This is a one-item 100-mm-long VAS and it is followed by an instruction to reflect on the sense of well-being during the last month. It has been translated into Norwegian for use in a similar population [54]. The scale’s anchoring points are ‘worst you have ever been’ (0) and ‘best you have ever been’ (100). AIOS has been found to be a valid measure for assessing well-being [77].*Sense of coherence*: To measure the participants’ sense of coherence, we will use the SOC-13 questionnaire. SOC-13 consists of 13 items with seven options for answers. The scoring ranges from 1 to 7, with a total score ranging from 13 to 91. A higher score indicates a stronger sense of coherence. The questionnaire has been translated and validated for a Norwegian context [78].*Physical ability*: As an objective measure of physical ability, we will use the 30-second chair to stand test. The test has been developed and validated for older adults [79] but has also been used and validated for wider populations [80–82].

#### Sample size

The translation of PAM into different languages has provided mean values for PAM in different populations [55, 83–85]. However, there is no common cut-off level for a clinically relevant change in PAM [86], and improvements in a PAM score after an intervention vary from 3 to 8 points [standard deviation (SD) 12–17] in different studies [54, 87–89]. Using a mixed linear model assuming a correlation within participants of 0.5, a difference between the groups at 12 months of 6 points, a SD of 13 [54], and a power of 80 %, the number needed in each arm becomes 55. To allow for dropout, the aim is to include 120 participants.

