### Interventions

#### Self-management course

The content of the self-management course includes theoretical education, group discussions based on the theoretical input, sharing of experiences and movement exercises. The staff developed the course based on recommendations found in the literature (e.g. [39–41]) and added elements from cognitive behavioural therapy focusing on the participants’ thoughts, emotions and actions. The theoretical part of the course comprises pain theory, barriers in everyday life due to chronic pain, problem-solving, goal-setting and techniques to deal with fatigue, poor sleep, frustrations and isolation. The movement exercises in each session aim to improve balance, posture and breathing, providing the participants with techniques to increase body awareness and the ability to relax. These techniques are essential in Norwegian psychomotor physiotherapy [42] on which this element of the course is built.

Guidelines for how to carry out the course have been developed to help the instructors, ensuring all groups are offered the same content and material (see Additional file 1).

The course is delivered as 2.5-hour weekly group workshops during the daytime for a period of 6 weeks, reaching a total of 15 hours, with 8–10 participants in each group. Two employees who have been dedicated to facilitating the course have a professional background as physiotherapists. All workshops start with the theoretical elements followed by the part of the course introducing movement exercises in a training room. Between the parts, there will be breaks for social interaction. Between each workshop, the participants will be given homework, e.g. working on their goal-setting plan.

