### Methodology for the RCT

#### Data collection

Data will be collected through self-report questionnaires at baseline (*t*_0_), and after 3 (*t*_1_), 6 (*t*_2_) and 12 months (*t*_3_). At baseline, the first author will be available for questions when the participants fill in the questionnaire. The first author will also supervise the physical ability test at baseline. Background variables such as age, gender, marital status, employment status, pain duration, referring institution, other diseases coded with the International Classification of Primary Care 2 (ICPC-2) [47], current medication and health-care utilisation will also be collected at baseline. At the three follow-up points (3, 6 and 12 months), the participants will be sent the questionnaires by mail. The participants will bring the completed self-administrated questionnaires to the follow-up visits, where a research assistant will supervise the physical ability test. There will be one postal reminder for each follow-up data collection point, and non-responders will be contacted by phone or email allowing a delay of up to 4 weeks.

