#### Statistical analysis

Outcome analyses will be conducted according to an intention-to-treat principle with mixed linear models. A mixed model accounts for repeated measures and potentially uses more of the data compared with an analysis of covariance. To account for within-subject correlations, participant ID will be specified as a random effect. The effect of intervention and time will be specified as a fixed effect with the levels ‘baseline’, ‘active 3 months’, ‘control 3 months’, ‘active 6 months’, ‘control 6 months’, ‘active 12 months’ and ‘control 12 months’.

In addition, a per-protocol analysis will be conducted, including participants who have been present at a minimum of three group sessions.

The confidence level is set to 95 %, and *p* ≤ 0.05 will be considered statistically significant. We will use Stata 14 [90], IBM SPSS 23 [91] and R version 2.13.1 [92] to analyse the data. A statistician blinded to group allocation will supervise the analysis.

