## Discussion

In summary, the trial’s design with the use of a qualitative approach alongside the RCT will enable us to address the knowledge gap, from multiple viewpoints, regarding easily accessible self-management interventions for people living with chronic pain.

One argument for courses offered at the HLCs in Norway is that they should be easily accessible. In this way, those in need of support for habit changes to achieve a healthy lifestyle, or to manage a chronic condition, can be reached [20]. Thus, to mirror the current practice and reach high external validity, the trial aims to recruit participants from the people targeted by the HLCs. However, this might be a challenge due to the need to include enough participants in the RCT to reach the required sample size within the trial’s timeframe. As seen in other studies, recruiting strategies may lead to different participants from those attending existing services [94]. Also, high attrition rates and a low uptake of self-management interventions have been seen in other studies [6]. Our trial has a broad recruitment strategy that might attract participants beyond those who would normally attend activities at the HLC. Nevertheless, the recruited group will have to fulfil the inclusion criterion of chronic pain and, thus, belong to the group of people who could benefit from engaging in their own health care, which is emphasised as society is seeing a rise in LTCs [5, 7, 10].

The intervention is developed from recommendations on self-management and chronic pain [39–41], together with the HLCs’ experiences from working with people in need of support to manage health issues and with people experiencing chronic pain in everyday life. Thus, the aim is to deliver an intervention that meets the needs of the target population and increases the participants’ ability to self-manage. The embedded qualitative approach will be used to explore how the participants experienced the different elements of the intervention. Together with the information from the questionnaires in the RCT, the qualitative study will make it possible to investigate if the intentions for the intervention are met and if there are any elements that ought to be changed.

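### The stated 80% power assumes independent participants and at most 8.3% loss at 12 months, while the course is given in groups and the planned model has no group term

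*Protocol article*

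**What the plan says.** The Sample size section of the protocol article assumes a within-participant correlation of 0.5, "a difference between the groups at 12 months of 6 points" and "a SD of 13 [54], and a power of 80" per cent. It concludes that "the number needed in each arm becomes 55. To allow for dropout, the aim is to include 120 participants". No dropout rate and no group-level correlation are given. The abstract repeats the 80%, the 55 and the 120.

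The Self-management course section describes weekly workshops over six weeks, "with 8–10 participants in each group", built on discussion and shared experience and facilitated by two dedicated physiotherapists. The Control group section plans groups of similar size, but attendance is voluntary and drop-in.

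The Statistical analysis section specifies a mixed linear model by intention to treat. Participant ID is the only random effect named, and the fixed effect has seven levels (a common baseline, then each arm at 3, 6 and 12 months).

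On attrition, the Discussion notes that "high attrition rates and a low uptake of self-management interventions have been seen in other studies", and the Background makes a similar remark. Under Data collection, questionnaires are mailed and "The participants will bring the completed self-administrated questionnaires to the follow-up visits". There is one postal reminder, and non-responders are contacted by phone or email.

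**The concern.** People who attend the same small discussion group with the same facilitators tend to have correlated outcomes. A sample size formula for independent individuals then overstates the information in the data. A mixed model that handles only the repeated measures within a person understates the standard error of the arm difference. Separately, a margin of five participants per arm is thin for a 12-month self-reported outcome in a field where the protocol itself reports attrition as a problem.

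Two things are at stake. If the analysis is left as written, confidence intervals are too narrow and a false positive is more likely than 5%. If the analysis is corrected for course group, power for a 6-point difference falls below the stated 80% over plausible values, and a null result would be given more weight than it deserves.

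**Working it through.** **Inputs from the protocol.** Difference 6, SD 13, correlation 0.5, power 80%, 55 per arm needed, 60 per arm included (Sample size). Two-sided 5%, implied by the 95% confidence level (Statistical analysis). Groups of 8–10, taken as 9. **Assumed, because the protocol gives neither:** ICC 0.02 and 0.05; 12-month loss of 15% and 20%, besides the implied 8.3%.

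**1. Reproducing the 55.** Unadjusted: n = 2 × (1.960 + 0.842)² × 13² / 6² = 73.7. Adjusted for baseline: 73.7 × (1 − 0.5²) = 55.3. At n = 55, SE = √(2 × 169 × 0.75 / 55) = 2.147 and power = Φ(6/2.147 − 1.96) = 79.8%. The planned seven-level mixed model, with equal correlations between visits and independent participants, gives the same 79.8%. An unadjusted comparison or a change score would need 74, and the mean of the three follow-ups about 31. The 55 therefore contains no allowance for clustering.

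**2. Dropout margin.** 1 − 55/60 = 8.3%.
- 15% loss: n = 51, SE 2.229, power 77%.
- 20% loss: n = 48, SE 2.298, power 74%.
- Earlier visits recover little: if every loss at 20% came after the 6-month visit, power would be 75.7%.

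**3. Clustering, with an analysis that accounts for course group.** DE = 1 + (m − 1) × ICC, with m = 9 × (1 − loss). The variance factor is DE if both arms are clustered, and (1 + DE)/2 if only the course arm is. SE is multiplied by the square root of the factor. Detectable difference = 2.80 × SE.

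Example: 15% loss, ICC 0.05, course arm only. m = 7.65, DE = 1.3325, factor 1.166, SE = 2.229 × √1.166 = 2.408. Power = Φ(6/2.408 − 1.96) = 70%; detectable difference = 2.80 × 2.408 = 6.7.

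| Loss | Clustered | ICC | Factor | Power | Detectable difference |
|---|---|---|---|---|---|
| 8.3% | course arm | 0.02 | 1.073 | 77% | 6.2 |
| 8.3% | course arm | 0.05 | 1.181 | 73% | 6.5 |
| 8.3% | both | 0.02 | 1.145 | 74% | 6.4 |
| 8.3% | both | 0.05 | 1.363 | 67% | 7.0 |
| 15% | course arm | 0.02 | 1.067 | 74% | 6.5 |
| 15% | course arm | 0.05 | 1.166 | 70% | 6.7 |
| 15% | both | 0.02 | 1.133 | 71.5% | 6.6 |
| 15% | both | 0.05 | 1.333 | 64.5% | 7.2 |

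**4. The model as planned.** It would use SE 2.229 at 15% loss although the true SE is larger by √factor. Type I error = 2Φ(−1.96/√factor). This gives 5.8% and 7.0% (course arm only, ICC 0.02 and 0.05), and 6.6% and 9.0% (both arms). The chance of a significant result for a true 6-point effect, Φ((6 − 1.96 × 2.229)/SE), stays at 74–76% in all four cases. In that model the fault shows mainly as false-positive risk.

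These are normal approximations with equal group sizes and the design effect applied to the baseline-adjusted variance. With 60/10 = 6 to 60/8 = 7.5 course groups, small-sample degrees of freedom would lower power somewhat further.

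**The case against.** Much of the case on the other side stands.

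- A reader might infer that the calculation is wrong. It is not: it reproduces, and only rounding 55.3 down to 55 could be faulted. The dispute is about assumptions.
- A reader might also infer that the trial certainly lacks 80% power. The protocol gives no ICC and no expected loss, so that cannot be said. With no clustering and no more than 8.3% loss, the stated power holds. With no loss at all, ICC 0.02 and only the course arm clustered (factor 1.08), power is still 80%.
- Full clustering in both arms is doubtful. The control activity is voluntary and drop-in, so stable groups of nine may not form. The course-arm-only rows are the more defensible ones, and they are the milder.
- The attrition remarks concern other studies, carry no percentage, and are partly about uptake of courses. Leaving a course is not the same as losing 12-month PAM data under intention to treat. The remarks sit uneasily with an 8.3% margin but do not contradict it.
- One might read the Data collection section as making the primary outcome depend on attending a visit. It does not say that. Mailing, a reminder and phone or email contact are all provided, so this is a minor point of wording.

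What does not fall away: group delivery of the course is fixed by design, neither the sample size inputs nor the stated model allows for it, and the dropout margin is small and unexplained.

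**Conclusion.** The point holds as one about assumptions and the analysis model. The 80% has no margin for course groups and covers only 8.3% loss. Over ICC 0.02–0.05 and loss of 8.3–15%, power with a group-adjusted analysis is about 70–77% if only the course arm is clustered and 64.5–74% if both are. Dropout alone, at 15–20%, gives 77–74%. The shortfall is moderate, and its size rests on assumed ICC and loss values.

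The likelier consequence of leaving the plan unchanged is not an over-read null result, as one might first suppose. It is a test run above its nominal 5%, because the planned model ignores course group. Restating power without changing the model would give figures that do not match the analysis.

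**What to change.** Keep the target of 120.

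1. In Statistical analysis, add a random effect for course group to the mixed model. Make it partially nested, with the group effect in the course arm only, because control attendance is drop-in. Use a small-sample degrees-of-freedom method, since there will be only about six to eight course groups.
2. In Sample size and the abstract, state the assumed ICC range and the expected 12-month loss, with the basis for each. Then give power and detectable difference at 120 over those values.
3. Optionally, state that PAM may be returned by post or taken by phone when a follow-up visit is missed.

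The cost is slightly wider confidence intervals, a less favourable stated power, some rewording, and a record of which course group each participant joined. Trial status reports that recruitment is still in progress, so the change can be made before the outcome analysis.

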#### Statistical analysis

Outcome analyses will be conducted according to an intention-to-treat principle with mixed linear models. A mixed model accounts for repeated measures and potentially uses more of the data compared with an analysis of covariance. To account for within-subject correlations, participant ID will be specified as a random effect. The effect of intervention and time will be specified as a fixed effect with the levels ‘baseline’, ‘active 3 months’, ‘control 3 months’, ‘active 6 months’, ‘control 6 months’, ‘active 12 months’ and ‘control 12 months’.

In addition, a per-protocol analysis will be conducted, including participants who have been present at a minimum of three group sessions.

The confidence level is set to 95 %, and *p* ≤ 0.05 will be considered statistically significant. We will use Stata 14 [90], IBM SPSS 23 [91] and R version 2.13.1 [92] to analyse the data. A statistician blinded to group allocation will supervise the analysis.

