#### Control group

Participants in the control group will be offered a drop-in outdoor easy physical activity, comprising walking and simple strength exercises. The activity will be adjusted to the participants’ physical ability, to keep it both easily accessible and rewarding. The rationale for choosing this activity is that the HLC already offers this activity as a drop-in service without registration or further commitment from people. Offering an activity to all participants in the trial is recognised as ethical and it is good clinical practice [43, 44]. Participation in the control group activity is voluntary, in line with the drop-in policy at the HLC.

The easy physical activity will be delivered as a weekly 1-hour session for a period of 6 weeks. The activity will be in groups with a group size similar to the intervention (8–10 participants in each group) and led by two instructors with skills in physical activity. The group will meet outdoors on a trail popular for walking among the municipality’s inhabitants. However, due to changing weather conditions and according to conditions on the trail, the location might be changed to another area during winter.

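### The stated model has a random effect for participant only, so any positive correlation within the delivery groups of 8–10 makes the standard error too small and lifts the error rate above 5%

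*Protocol article*

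**What the plan says.** The protocol article randomises individuals, stratified by gender (Randomisation and allocation).

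The course runs weekly for six weeks, "with 8–10 participants in each group". Its content includes "group discussions based on the theoretical input, sharing of experiences and movement exercises" (Self-management course). On staffing, the same section says: "Two employees who have been dedicated to facilitating the course have a professional background as physiotherapists".

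For the comparator, the Control group section says: "The activity will be in groups with a group size similar to the intervention (8–10 participants in each group". It adds: "Participation in the control group activity is voluntary, in line with the drop-in policy at the HLC".

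The Statistical analysis section sets out a mixed linear model. Its random part is "To account for within-subject correlations, participant ID will be specified as a random effect". For the fixed part it says "The effect of intervention and time will be specified as a fixed effect with the levels" and then lists seven: one shared baseline, and each arm at 3, 6 and 12 months. Significance is judged at p ≤ 0.05.

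The Sample size section assumes a 6-point difference at 12 months, an SD of 13, a within-participant correlation of 0.5 and 80% power. It arrives at 55 per arm, with 120 participants in all to allow for dropout. No section mentions a group effect, an ICC, a design effect or a cluster-robust variance.

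**The concern.** People who go through a six-week discussion course together share the mix of personalities, the timing and the quality of the exchange. Their later outcomes may resemble each other more than those of people from different groups. Instructors are even asked to report on the dynamics of each group (Documentation of the delivery of the intervention), so the protocol itself treats the group as a unit that can vary.

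A participant random effect absorbs correlation between visits of one person. It does nothing for correlation between two people in the same group. If such correlation exists, there is less independent information than the model assumes. Confidence intervals would then be too narrow and the false-positive rate above 5%. This would affect the 12-month PAM contrast for which the trial is sized, and the secondary outcomes analysed with the same model.

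**Working it through.** **Inputs from the protocol.** Group size 8–10 (midpoint 9); difference 6; SD 13; within-participant correlation 0.5; power 80%; 55 per arm, 60 per arm recruited. The 5% level is taken as two-sided, in line with the 95% confidence level.

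**Assumed input.** Group ICC of 0, 0.01, 0.02, 0.05 or 0.10. The protocol gives none.

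**Step 1: reproduce the 55.** Two-sample formula: 2 × (13 × (1.960 + 0.842)/6)² = 73.7 per arm. Adjustment for baseline with correlation 0.5 multiplies this by 1 − 0.5² = 0.75, which gives 55.3. This matches the stated 55 (power at 55 per arm is 79.8%). All participants are treated as independent here, so the figure contains no allowance for groups.

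**Step 2: true error rate of the unadjusted test.** If both arms cluster equally, the design effect is DE = 1 + (m − 1) × ICC, which for m = 9 is 1 + 8 × ICC. If only the course arm clusters, the average over the two arms is (1 + DE)/2 = 1 + 4 × ICC. The true two-sided error is 2 × (1 − Φ(1.96/√DE)). Example at ICC 0.05, both arms: DE = 1.40, 1.96/√1.40 = 1.656, error 9.8%. The reported standard error is then 1/√1.40 = 0.845 of the true one.

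| ICC | DE, both arms | Error | Average DE, course only | Error |
|---|---|---|---|---|
| 0 | 1.00 | 5.0% | 1.00 | 5.0% |
| 0.01 | 1.08 | 5.9% | 1.04 | 5.5% |
| 0.02 | 1.16 | 6.9% | 1.08 | 5.9% |
| 0.05 | 1.40 | 9.8% | 1.20 | 7.4% |
| 0.10 | 1.80 | 14.4% | 1.40 | 9.8% |

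**Step 3: simulation of the stated model, no true effect, group effects after baseline only.**

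| ICC | A: both arms | B: both arms | B: course only |
|---|---|---|---|
| 0 | 5.3% | 5.5% | 5.2% |
| 0.01 | 6.1% | 6.1% | 5.3% |
| 0.02 | 6.9% | not run | not run |
| 0.05 | 10.9% | 12.4% | 9.2% |
| 0.10 | 15.3% | 19.4% | 12.3% |

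A: 60 per arm, 7 groups per arm, 6,000 trials per ICC. B: 54 per arm, groups of 9, 2,000 trials per setting, ICC as a share of the unadjusted variance 13² = 169.

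B exceeds the formula from ICC 0.05 upwards for two reasons. Baseline adjustment shrinks the individual variance to 169 × 0.75 = 126.75 but leaves the group variance whole. The model also absorbs the group effect into the participant effect and so overstates the gain from baseline. At ICC 0.05 with both arms clustered, B's mean model standard error was 2.12 against an empirical 2.64.

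**Step 4: power with a correct standard error, 55 per arm, groups of 8–10.** The required number is 55.3 × DE.

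| ICC | Power, both arms | Power, course only |
|---|---|---|
| 0.01 | 76–77% | 78% |
| 0.02 | 73–75% | 76–77% |
| 0.05 | 64–67% | 71–73% |
| 0.10 | 53–57% | 64–67% |

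For 80% power at ICC 0.05 the requirement is 75–81 per arm (both arms) or 65–68 (course only). These are normal approximations; with few groups the true power is slightly lower.

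**Step 5: number of groups.** 55/9 = 6.1 and 60/9 = 6.7, so about 6–7 per arm.

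**The case against.** The protocol has several features that should keep the ICC low. There is one centre. Two dedicated physiotherapists facilitate the course, under guidelines meant to give every group the same content. The contrast used for sizing comes at 12 months, long after a six-week course. At an ICC of 0.01–0.02 the distortion is modest: 5.5–6.9% by formula. All of this stands as a reason not to assume a large ICC. It does not make the ICC zero, because common staff and guidelines do not remove differences due to group composition, peer discussion and timing.

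The control arm is the weaker part of the case. A reader might infer that both arms consist of fixed groups with equal clustering. The protocol does not say so. It plans control groups of 8–10 but describes a voluntary drop-in activity of walking and simple strength exercises, with no stated counterpart to the course's discussion. Stable membership there is an inference, so the both-arm figures are not the only relevant ones.

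It can also be said that the article never states that participant is the sole random effect, and that an analysis plan may add a group term. That carries less weight. The section names the random effect, gives its purpose and lists every fixed-effect level, and the sample size reproduces only under independence. The point rests on a model that is stated, not on a detail left open.

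**Conclusion.** The point holds conditionally. For any positive group ICC, the stated model gives too small a standard error for the PAM contrast and a true error rate above 5%. For assumed ICCs of 0.01 to 0.10 and groups of 9, the formula gives 5.9% to 14.4% if both arms cluster equally and 5.5% to 9.8% if only the course arm does. Simulated values are higher at 0.05 and above.

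Two stronger conclusions are not supported. One is that the 5% level is certainly breached: the protocol contains no ICC, and at ICC 0 nothing changes. The other is that one or two good groups could by themselves produce a positive result: nothing calculated here shows that.

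**What to change.** - Record the allocated group for every participant, and keep non-attenders in that group.
- Add a random effect for group that acts on the 3-, 6- and 12-month records only, because groups form after randomisation.
- If control participants do not attend as stable groups, use a partially nested form with the group effect in the course arm only. Decide this before outcome data are seen.
- Use a Satterthwaite or Kenward–Roger degrees-of-freedom correction, since about 6–7 groups per arm estimate the group variance poorly.
- Report the estimated ICC.
- State in the Sample size section that 55 per arm gives 80% power only under independence, with the figures for an assumed ICC. At 0.05 these are about 64–67% with both arms clustered and 71–73% with the course arm only.

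The cost is one group identifier, one model term, a somewhat wider interval and a lower stated power. The Trial status section says recruitment was still in progress, so the change could be made before analysis. Made later, it could look driven by the data.

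### The analysis model handles within-participant correlation only by a participant random effect, so the 12-month standard error is well calibrated only if correlation and variance stay constant over the year

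*Protocol article*

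**What the plan says.** Under Statistical analysis, the article gives its means of handling correlation within a participant: "participant ID will be specified as a random effect". It mentions no random slope, residual covariance structure or robust standard error. On the mean structure it is fuller: "The effect of intervention and time will be specified as a fixed effect with the levels" and then lists seven levels, namely one baseline shared by both arms and separate active and control levels at 3, 6 and 12 months.

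Under Sample size, the number per arm comes from a mixed linear model "assuming a correlation within participants of 0.5", with an SD of 13, 80% power and "a difference between the groups at 12 months of 6 points". One correlation and one SD are given, with no distinction between visits. Under Data collection, the visits are at baseline, 3, 6 and 12 months, so pairs of visits lie between 3 and 12 months apart.

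**The concern.** A participant random intercept with independent, equal-variance residuals is compound symmetry: all four visits share one variance, and all six pairs of visits share one correlation. With a shared baseline, the model adjusts the 12-month arm difference for the chance baseline difference, using the common fitted correlation as the slope. That fitted value averages over all pairs, most of them closer together than baseline and 12 months.

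If correlation weakens as visits move apart, the average exceeds the baseline-to-12-month correlation. The model then credits the 12-month contrast with more precision than it has. This contrast is the one the trial is sized on, and it uses the pair of visits furthest apart. At stake is whether its 95% interval and p-value have their nominal properties.

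**Working it through.** **Inputs from the article.** Difference 6 PAM points at 12 months, SD 13, correlation 0.5, power 80%, 55 per arm. The article does not say that the test is two-sided; I take this from "The confidence level is set to 95" per cent.

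**Step 1: reproduce the plan's figure.** For a baseline-adjusted 12-month comparison,

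n = 2 × (13 × (1.960 + 0.842) / 6)² × (1 − 0.5²) = 73.69 × 0.75 = 55.27 per arm.

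This agrees with the stated 55 (power at 55 is 79.8%). The 0.5 in this formula acts as the baseline-to-12-month correlation.

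**Step 2: reported against true variance, equal SDs, complete data.** Let r be the fitted common correlation and q the true baseline-to-12-month correlation. The estimator is (12-month difference) − r × (baseline difference). In units of 2 × SD² / n:

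- variance reported by the model: 1 − r²
- true variance: 1 + r² − 2rq

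The two agree only if r = q. The SE multiplier is √(true / model), and the actual two-sided error is 2 × [1 − Φ(1.96 / multiplier)].

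**Step 3: numbers.** Every pattern other than constant 0.5 is an assumption.

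| Assumed pattern | r | q | True | Model | SE multiplier | Type I error |
|---|---|---|---|---|---|---|
| Constant, as planned | 0.50 | 0.50 | 0.750 | 0.750 | 1.00 | 5.0% |
| A: mild fall | 0.525 | 0.45 | 0.803 | 0.724 | 1.05 | 6.3% |
| B: q as planned, other pairs higher | 0.60 | 0.50 | 0.760 | 0.640 | 1.09 | 7.2% |
| C: larger fall | 0.583 | 0.40 | 0.873 | 0.660 | 1.15 | 8.8% |

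Pattern A has baseline correlations 0.55, 0.50 and 0.45 with 3, 6 and 12 months, and 0.60 (3–6), 0.50 (3–12) and 0.55 (6–12); the mean is 3.15 / 6 = 0.525. In PAM points, pattern C gives a reported SE of 13 × √(2 × 0.660 / 55) = 2.01 against a true 13 × √(2 × 0.873 / 55) = 2.32.

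**Step 4: let the 12-month SD differ.** Take pattern A with SD 13 at the first three visits. The common variance s² is the mean of the four variances, and r is the mean covariance divided by s². The model variance is s²(1 − r²); the true one is SD12² + r² × 169 − 2r × 0.45 × 13 × SD12.

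- SD12 = 12: s² = (3 × 169 + 144) / 4 = 162.75; r = (1.65 × 169 + 1.50 × 156) / 6 / 162.75 = 0.525. True 116.9, model 117.9, multiplier 0.996, type I error 4.9%.
- SD12 = 15: s² = (3 × 169 + 225) / 4 = 183; r = (1.65 × 169 + 1.50 × 195) / 6 / 183 = 0.520. True 179.4, model 133.4, multiplier 1.16, type I error 9.1%.

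A one-point fall in SD at 12 months thus removes the problem in pattern A, and a two-point rise makes it clearly worse. Both SDs lie within the 12–17 that the article cites across studies, but that range says nothing about change between visits within this trial.

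**Step 5: cost to the estimate itself.** With complete data, randomisation keeps the contrast unbiased whatever r is. Compared with the optimal adjustment (variance 1 − q²), the true SE rises by √(0.760 / 0.750) = 1.007 in pattern B and √(0.873 / 0.840) = 1.02 in pattern C. Almost all of the effect is therefore in the reported SE and hardly any in efficiency.

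**The case against.** The case against has real weight.

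- **The article does not say intercept only.** A reader might infer that it commits to compound symmetry. It states a participant random effect and is silent on residual covariance and the type of standard error. An analysis plan that is not shown may settle these, and a condensed article may leave them to it. This stands as a limit. Yet the sentence on within-subject correlation is a positive statement that names one device, so it is fair to comment on what that device implies with ordinary residuals.
- **Nothing in the article shows falling correlation.** A reader might infer that the 12-month interval will be too narrow. The documents do not support that: at the stated 0.5 held constant there is no error, and the SD example shows that the sign can change. Steeper assumed patterns give larger figures. For example, exponential decay in months reaching 0.5 at 12 months has r = 0.698 and a multiplier of √(0.789 / 0.513) = 1.24, with a type I error of 11.4%. There is no basis in the article for choosing such a pattern.
- **No stated figure is wrong.** A reader might infer that the sample size or the estimate is faulty. The 55 per arm reproduces, and the estimate is unbiased with complete data.
- **Dropout.** Likelihood-based handling of missing visits relies on the covariance being right, but that is a general property of the method. I attach no size to it here.
- **The model is common and defensible.** True; the point is a robustness improvement and not the correction of an error.

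**Conclusion.** The point holds in conditional form. Read with ordinary residuals, the stated model gives a correctly calibrated 12-month interval under constant variance and correlation, an assumption that the article neither states nor defends for visits 3 to 12 months apart. With equal SDs and a baseline-to-12-month correlation of 0.40 to 0.50 lying below a pooled value of 0.525 to 0.60, the reported SE is too small by a factor of about 1.05 to 1.15, and a nominal 5% test runs at about 6% to 9%. These patterns are assumed, and a change in the 12-month SD can enlarge, cancel or reverse the effect. What is in doubt is the calibration of the interval and p-value for the contrast on which the trial is sized. It is worth changing because the remedy costs little and removes the dependence on an assumption that cannot be checked before the data are in.

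**What to change.** Keep the seven-level fixed effect with the shared baseline. Replace the participant random effect by an unstructured four-by-four within-participant covariance, with a small-sample degrees-of-freedom correction such as Kenward-Roger or Satterthwaite. State in advance that, if this model does not converge, the random-intercept model will be used with robust standard errors.

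This is about one sentence in the analysis section. It means ten covariance parameters instead of two, for a target of 120 participants, and a convergence rule written down beforehand. Visits, estimand and sample size stay as they are: the unstructured model adjusts by the baseline-to-12-month correlation itself, which is the quantity that the 0.5 represents in the sample-size formula. Settling this before the data are analysed also avoids choosing a covariance after seeing results.
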